### Participant timeline

Potentially eligible women receive a study flyer when registering with one of the participating maternity care organizations. During a scheduled home visit (i.e. the intake), the participant will fill out the structured risk assessment electronically. At the end of the standard maternity care provision period, a second questionnaire will be filled out assessing the primary outcome and a number of secondary outcomes (Table 3). A third electronic questionnaire will be sent to participants during the late postpartum period (i.e. six weeks after they gave birth). This questionnaire will assess multiple secondary outcomes (Table 3).

### Sample size

Calculation of sample size is based on the presumed effect of the intervention on the primary outcome at the individual level. The intervention is considered to be effective when the prevalence of a low empowerment score, is reduced by 50%; in other words, our sample size is calculated to determine a proportion difference from a low empowerment score at the 20th centile towards the 10th centile.

A previous study using the MEQ, in an unselected population of 2675 women in the postpartum period, showed a mean score over four domains of 3.70, with a left-skewed distribution (25th centile 3.46 and 75th centile 3.88) [20]. We hypothesize that the intervention will lead to a decline of an empowerment score of < 3.38 (i.e. the 20th centile) by 50%. At an alpha of 0.05 and 80% power, we will require 196 participants per arm and as such 392 participants in total.

The intervention will be implemented at the cluster level (i.e. (groups of) maternity care organizations), while the intervention effect will be assessed at the participant level. We expect a small variance in provided care between clusters as is common in primary care practices [21]. The Intraclass Correlation Coefficient (ICC) is therefore set at 0.05. The Variance Inflation Factor (VIF), calculated with the formula of Donner et al. [22], is calculated to be 2.91.

We account for a lost to follow-up of 33% (i.e. from inclusion to assessment of primary outcome). The target sample size is therefore set at 856 (i.e. 1.5*(2.91*196)) participants per arm.

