### Study setting

This study is embedded in the HP4All-2 program that aims to reduce perinatal health inequalities and to improve the care for young children and their mothers [17]. Six out of ten participating municipalities within the overall HP4All-2 program participate in this trial. A detailed description of the selection process of municipalities has been published before [17]. We designed a two-arm C-RCT in six municipalities, including 12 maternity care organizations (Fig. 1). Two adjacent municipalities were merged to ensure that enough eligible women could be expected to be included during the study period. The resulting five participating municipalities were each subdivided into an intervention cluster and a control cluster, resulting in a total number of ten clusters. Each cluster consisted of one or more distinct maternity care organizations, depending on the expected number of eligible women within each organization (Fig. 1). Clustering at the level of the maternity care organization was chosen to avoid contamination of the intervention, which includes education of MCAs, between MCAs within maternity care organizations and between mother-baby dyads cared for by the same MCA. Outcomes will be assessed at the individual level.

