### Statistical methods

All analyses will be performed according to the intention-to-treat principle.

Descriptive statistics will be presented, and formal inference will be based on hypothesis testing with two-sided statistical significance assessed at the 5% level.

Multiple imputation using chained equations will be used to account for missing data in baseline characteristics. We will analyze the effect of the intervention on our primary and secondary outcome measurements using multilevel mixed-effects linear or logistic regression analyses with an assumed random effect for each cluster.

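### The design effect of 2.91 is taken at about 39 women per cluster, but the trial will analyse about 114; at the stated ICC, ten clusters give about 46% power, not 80%

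*Protocol article*

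**What the plan says.** The Sample size section of the protocol article powers the trial on "a proportion difference from a low empowerment score at the 20th centile towards the 10th centile". Before clustering it states: "At an alpha of 0.05 and 80% power, we will require 196 participants per arm and as such 392 participants in total". It then fixes the clustering assumption, "The Intraclass Correlation Coefficient (ICC) is therefore set at 0.05", and reports a variance inflation factor that "is calculated to be 2.91". The mean cluster size behind that factor is not printed. With 33% loss allowed for as a multiplier of 1.5, the section concludes: "The target sample size is therefore set at 856 (i.e. 1.5*(2.91*196)) participants per arm".

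The Study setting section gives the number of clusters. Five municipalities (after one merger) are each divided into an intervention and a control cluster, "resulting in a total number of ten clusters", which is five per arm. The Statistical methods section specifies "two-sided statistical significance assessed at the 5% level" and mixed-effects models with a random effect per cluster.

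**The concern.** The design effect depends on the number of women analysed per cluster. If the total is multiplied by a design effect while the number of clusters stays fixed, every cluster grows, and the design effect just used no longer applies. A factor of 2.91 fits clusters of about 39 women. The target it produces implies clusters of about 114.

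At stake is the power for the primary outcome. The recruitment target of 1,712 women is justified by a calculation that the design does not satisfy at its own ICC. If the trial finds no difference, the reader needs to know that it had less than an even chance of detecting its target effect.

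**Working it through.** **Inputs.** 20% versus 10%, 80% power, ICC 0.05, factor 2.91, loss multiplier 1.5 and 856 per arm (Sample size); two-sided 5% (Statistical methods); ten clusters, five per arm (Study setting).

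**1. Reproducing the plan's figures.**
- Individual randomisation, unpooled variance: n = (1.96 + 0.8416)² × (0.16 + 0.09) / 0.10² = 196.2 per arm. This agrees with 196.
- Design effect = 1 + (m − 1) × ICC. With m = 392/10 = 39.2, it is 1 + 38.2 × 0.05 = 2.91, an exact match. Using the 12 organisations would give 2.58, and the 17 sites mentioned in the Discussion would give 2.10.
- 1.5 × 2.91 × 196 = 855.5, rounded to 856.

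So the arithmetic reproduces, with the design effect taken at the cluster size before inflation.

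**2. Design effect at the size the trial will have.**
- Analysed per arm: 856/1.5 = 570.7. Per cluster: 570.7/5 = 114.1.
- Design effect: 1 + 113.1 × 0.05 = 6.66.
- Effective sample: 570.7/6.66 = 85.7 per arm, against the 196 required.

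**3. Power for 20% versus 10%.**
- z = 0.10/√(0.25/85.7) = 1.85.
- Normal approximation: Φ(1.85 − 1.96) = 45.7%. With a pooled variance under the null it is 44.9%.
- Noncentral t on 8 df (ten clusters minus two): 37.1%.

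**4. Can more women repair it?** As m grows, the effective sample per arm approaches k/ICC, where k is the number of clusters per arm. Here that is 5/0.05 = 100 per arm, so power cannot exceed 51.6% (normal) or 42.1% (8 df). An effective sample of 196 needs k > 196 × 0.05 = 9.8 clusters per arm.

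**5. ICC at which 80% would hold.** Solving 570.7/(1 + 113.1 × ICC) = 196 gives ICC = 0.017. On 8 df the threshold is about 0.011.

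| ICC | Design effect | Effective n per arm | Power, normal | Power, t on 8 df |
|---|---|---|---|---|
| 0.01 | 2.13 | 268 | 91% | 82% |
| 0.017 | 2.92 | 195 | 80% | 69% |
| 0.03 | 4.39 | 130 | 63% | 52% |
| 0.05 | 6.66 | 86 | 46% | 37% |

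**6. Detectable effect at ICC 0.05.** With 80% power, the fall would have to be from 20% to about 6% (normal) or about 4.4% (8 df), against the planned 10%.

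**7. Sensitivity to the count of units.** Counting 12 organisations (six per arm) gives an effective sample of 100 and 52% power, with a ceiling of 120. Counting 17 sites (8.5 per arm) gives 132 and 63%, with a ceiling of 170. Both ceilings are below 196. With no loss at all (171 women per cluster), power in ten clusters is still only about 47%.

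**The case against.** The strongest objection concerns pairing. Each municipality contributes one intervention and one control cluster. If the analysis exploited those pairs, only the between-cluster variance within municipalities would count against the comparison. If pairing removed about two-thirds of that variance (from 0.05 to about 0.017), the effective sample would return to about 196 per arm. It is therefore too strong to say that ten clusters could never reach 80% under any analysis.

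This limits the wording but does not rescue the plan. The Sample size section takes no credit for pairing and applies 0.05 unadjusted. The Statistical methods section specifies only a random effect per cluster. The share of variance that pairing would remove is unknown. A paired analysis of five pairs would also leave only 4 df, on which power in that favourable scenario is about 56%.

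Two smaller points are fair. The cluster size of 39.2 is inferred, although the match is exact and the other unit counts in the article do not fit. The 80% is attached in words to the 196-per-arm step, and that 856 preserves it is implied, though that is plainly the purpose of the inflation.

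**Conclusion.** The concern holds. The factor 2.91 belongs to clusters of about 39 women, and the trial as planned will analyse about 114 in each of ten clusters. At the protocol's own ICC of 0.05 and with the unpaired model it describes, power is about 46% (normal approximation) or 37% (8 df). It cannot pass 52% at any enrolment.

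These figures assume equal cluster sizes, one-third loss and a simple comparison of 20% with 10%; unequal clusters would lower them. The 8 df reference is an assumption of this check, since the article states no small-sample method. The normal figure is the more favourable of the two and is on the same basis as the plan's 196.

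**What to change.** In the Sample size section:

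- Replace the factor of 2.91 with the design effect at the analysed cluster size: 1 + (114 − 1) × 0.05, about 6.66.
- State the power of 856 per arm in five clusters per arm: about 46% (37% on 8 df) at ICC 0.05.
- Give the table of power by ICC with both columns, because the normal approximation alone is optimistic with ten clusters.
- Make any 80% claim conditional: ICC at most about 0.017 by the normal approximation, or about 0.011 on 8 df. If a lower ICC is to be relied on, or credit taken for pairing by municipality, justify it there and match it in the analysis model.

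This costs a rewording and a less favourable stated power, with no extra participants. It discloses the shortfall without removing it. Reaching 80% at ICC 0.05 under the unpaired model would need at least ten clusters per arm, and more in practice: at exactly ten, 196 × 0.95/(1 − 9.8/10) = 9,310 analysed women per arm would be required.

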### Recruitment

To achieve adequate participant enrolment, an inclusion target per month will be set for each organization. Monitoring of this target will be communicated on monthly bases with all local researchers. Not achieving this target is seen as the impediment of effective recruitment and action will be taken to improve the effectiveness in recruiting eligible participants. An example of such action would be evaluating the barriers for participant inclusion, evaluating engagement barriers, and providing additional support for MCAs.

### Randomization and allocation

We will perform allocation by clusters, with the maternity care organization(s) as the randomization unit, to minimize possible contamination effects among professionals. Each cluster was randomized to the intervention arm or the control arm by a statistician not involved in the implementation of the trial and blind to the identity of the clusters and the incorporated maternity care organizations.

### Blinding

Maternity care organizations agreed to participate, and to accept any allocation, prior to the randomization procedure.

Study information to participants strictly contains information related to the allocated arm, without mentioning the randomized design of the trial or the changes in the provided care during pregnancy and the postpartum period.

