#### Criteria for health care professionals

MCAs from the participating organizations will act as local researchers after completing the training sessions. They will inform potential participants about the study and obtain written informed consent. They also serve as the main point of contact between the research team and the participants, and have a key role in sustaining participant recruitment and participant participation throughout the study period.

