#### Exclusion criteria participants

Unwillingness to sign a written informed consent form.

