#### Control situation

To adequately compare the intervention and the control group with regard to their medical and non-medical risk factors during pregnancy, the risk assessment during pregnancy is performed in both study arms. The MCA in the control arm is however instructed not to discuss the detected risks with the participant upon completion of the risk assessment or to discuss the findings with other health care professionals. One exception to this blinding of participants is made for the risk factor “suicidal thoughts”, given the severity of this risk identification. In the control group the risk assessment will be followed by conventional care during pregnancy and the postpartum period.

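### Women are enrolled after cluster allocation by care assistants who know their arm, using information tied to that arm, so who consents can differ between arms

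*Protocol article*

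**What the plan says.** All places are in the Methods of the protocol article.

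- **Unit and timing of allocation** (Randomization and allocation): "We will perform allocation by clusters, with the maternity care organization(s) as the randomization unit". The act itself is reported as done: "Each cluster was randomized to the intervention arm or the control arm by a statistician not involved in the implementation of the trial".
- **Who agreed beforehand** (Blinding): "Maternity care organizations agreed to participate, and to accept any allocation, prior to the randomization procedure". Nothing comparable is said of the women.
- **Who recruits** (Criteria for health care professionals), of the MCAs: "They will inform potential participants about the study and obtain written informed consent".
- **What women are told** (Blinding): "Study information to participants strictly contains information related to the allocated arm", and this is done "without mentioning the randomized design of the trial or the changes in the provided care during pregnancy and the postpartum period".
- **What the recruiter knows** (Control situation): "The MCA in the control arm is however instructed not to discuss the detected risks with the participant upon completion of the risk assessment". Under Intervention, by contrast, the MCA goes through the identified risks with the woman and follows care pathways. MCAs in intervention organisations also get an extra training session.
- **Who is kept out** (Exclusion criteria participants): "Unwillingness to sign a written informed consent form". This is the only criterion listed.
- **Analysis** (Statistical methods): intention-to-treat, with multilevel linear or logistic models. The only model term named is a random effect for cluster. Missing baseline characteristics are to be imputed.

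**The concern.** Randomising clusters balances the organisations, up to chance. It balances the women only if those who enter are identified and consent independently of the arm. Here the recruiter knows the arm, the information is tied to the arm, and consent alone decides entry.

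If vulnerable women accept more or less readily in one arm, or if an MCA presents the study differently because of what she will or will not do with the results, the enrolled groups differ before any treatment effect. The article's Introduction links low socioeconomic status to lower empowerment, and the trial targets deprived neighbourhoods. Selection on vulnerability would therefore act directly on the primary outcome.

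Women who decline are not in the analysis set, so intention-to-treat does not help. A larger sample does not reduce such a bias; it only makes a spurious difference easier to declare significant.

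**Working it through.** **Order of events.** The article gives no dates, so the order is inferred from two facts. Randomisation is described in the past tense and enrolment in the future tense. Information specific to an arm also cannot be handed out before the arm is known. The sequence is then:

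1. Organisations agree.
2. Clusters are randomised.
3. Women register and receive a flyer.
4. The MCA informs the woman and obtains consent around the home visit.
5. The woman completes the intake assessment.
6. The MCA discusses the results or, in the control arm, does not.

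The article describes no step that makes step 4 independent of step 2, such as a recruiter unaware of the arm, identical information in both arms, or individual consent before allocation.

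**The plan's own figures.** These are not in dispute, but they set the scale.
- Target: 20% versus 10%, two-sided 5%, 80% power. n = (1.960 + 0.842)² × (0.20×0.80 + 0.10×0.90) / 0.10² = 196.2, against the stated 196 per arm.
- Variance inflation: 1 + 0.05 × (196/5 − 1) = 2.91, as stated.
- Target per arm: 1.5 × 2.91 × 196 = 855.5, stated as 856.

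The target difference is thus 10 points, and the effective size the plan aims for is 196 per arm.

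**Simple illustration (all inputs assumed).** Take a low-empowerment prevalence of 32% in women with non-medical risk factors and 12% in those without, and no treatment effect. Suppose 50% of enrolled women carry risk factors in the intervention arm and 40% in the control arm.
- Intervention: 0.5×0.32 + 0.5×0.12 = 22%.
- Control: 0.4×0.32 + 0.6×0.12 = 20%.
- Difference: 2 points, one fifth of the target, and against the intervention.

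**Range (all inputs assumed except the 20% and the 196).** Let 30% of eligible women be vulnerable. Consent is 70% everywhere except among vulnerable women in the intervention arm, where it is c. Control prevalence is 20%, which matches the outcome definition (below the control arm's 20th centile). There is no true effect. With risk r in vulnerable women, risk in the others is s = (0.20 − 0.30r)/0.70, and

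p₁ = (0.30·c·r + 0.70·0.70·s) / (0.30·c + 0.70·0.70).

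Example, r = 0.35 and c = 0.50: s = 0.1357; p₁ = (0.0525 + 0.0665)/0.64 = 18.6%; difference −1.4 points. The last column is Φ(d − 1.96) + Φ(−d − 1.96), with d = (0.20 − p₁)/√[(0.20×0.80 + p₁(1 − p₁))/196].

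| r | s | c | p₁ | Spurious difference (points) | Chance of a significant result |
|---|---|---|---|---|---|
| 35% | 13.6% | 60% | 19.3% | −0.7 | 5.3% |
| 35% | 13.6% | 50% | 18.6% | −1.4 | 6.4% |
| 35% | 13.6% | 35% | 17.4% | −2.6 | 10.3% |
| 35% | 13.6% | 90% | 21.2% | +1.2 | 6.0% |
| 45% | 9.3% | 60% | 18.9% | −1.1 | 5.9% |
| 45% | 9.3% | 50% | 17.7% | −2.3 | 9.1% |
| 45% | 9.3% | 35% | 15.6% | −4.4 | 20.8% |
| 45% | 9.3% | 90% | 22.0% | +2.0 | 7.7% |

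Modest differences in consent do little harm. Serious inflation needs consent among vulnerable women to be halved in one arm together with a strong link to the outcome.

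**The case against.** The protocol has real safeguards.

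- The information leaves out the changes in care as well as the randomised design. A reader might infer from the words about the allocated arm that intervention women are offered help on paper while control women are offered only a questionnaire. The full sentence does not support that. The texts are not shown, and how far they differ is unknown. The omission probably reduces differential consent by the women themselves.
- All women with a scheduled home visit are to be invited, so MCAs have no stated discretion over whom to approach. The first contact is a flyer at registration, and administrative staff are trained to send it, schedule the intake and inform women.
- Both arms within a municipality are trained together, including in how to include participants correctly.
- The same risk assessment is done in both arms expressly so that their risk factors can be compared.
- Imputing baseline characteristics suggests, without saying so, that they enter the models. A covariate list may also sit in an analysis plan that is not shown.

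All of this stands as mitigation. It does not blind the person taking consent or make the information the same in both arms. Inviting everyone does not equalise acceptance or the way the study is presented. The intake comparison covers only women who consented, and only what was measured. The independent statistician, blind to cluster identity, protects the allocation of clusters but not the later recruitment of individuals.

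**Conclusion.** The point holds as a risk built into the design: consent can depend on allocation, and no step described in the article removes that dependence. It rests on stated facts, plus the inference that enrolment follows allocation.

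The documents do not show that consent will differ, in which direction, or by how much. The 2-point figure and the range of −4.4 to +2.0 points are illustrations on assumed risks and consent rates and should not be read as estimates of bias in this trial. The bias could flatter the intervention or count against it.

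The point merits action because the remedies are cheap and the baseline data are already being collected.

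**What to change.** 1. **Adjust the primary analysis.** In the mixed-effects logistic model under Statistical methods, add the intake Maternal Empowerment Questionnaire score and the main intake risk factors as prespecified covariates. They are collected in both arms before results are discussed. The intake version omits two of the five domains, including one that counts towards the outcome, but it remains usable as a covariate. If the analysis plan already lists these covariates, this item is met. Adjustment does not remove selection on unmeasured factors.
2. **Use one text.** Where enrolment is still open, replace the arm-specific information with a single flyer and consent text for both arms, limited to the elements they share: the intake questionnaire and the follow-up questionnaires. It should not say that results may be used in care, because the control instruction restricts this.
3. **Make enrolment visible.** Report eligible and consenting women by cluster from the organisations' registration lists. This is a reporting step; it exposes differential enrolment but does not correct it.

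Cost: an ethics amendment for the text, a count from the registration lists, and minor extra analysis work. If enrolment has closed, items 1 and 3 remain possible.

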### Data collection

No interim analyses are planned, and all outcomes will be analyzed following data collection.

### Statistical methods

All analyses will be performed according to the intention-to-treat principle.

Descriptive statistics will be presented, and formal inference will be based on hypothesis testing with two-sided statistical significance assessed at the 5% level.

Multiple imputation using chained equations will be used to account for missing data in baseline characteristics. We will analyze the effect of the intervention on our primary and secondary outcome measurements using multilevel mixed-effects linear or logistic regression analyses with an assumed random effect for each cluster.

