### Intervention

#### Intervention at the level of the participant

The intervention consists of two dimensions: 1) a systematic risk assessment during pregnancy with emphasis on identification of non-medical risk factors for adverse maternal and neonatal health outcomes, and 2) subsequent adaptation of maternity care towards a client-tailored approach during pregnancy and the postpartum period.

The first part is based on an electronic risk assessment questionnaire and covers six different domains related to individual level SES and psychological factors. All assessed factors are known to be associated with adverse health outcomes during pregnancy, childbirth or early childhood. The assessment consists of three main components: 1) the validated Mind2Care (M2C) tool [19], 2) the Maternal Empowerment Questionnaire (MEQ) [20] with slight modifications, and (3) eight additional questions regarding a person’s financial situation, whether they have health care insurance, and their use of health care in the year prior to pregnancy. Two out of five domains of the MEQ were omitted for this assessment after consulting the authors (i.e. domains “the future” and “maternity care”) as being not applicable. All other questions were grammatically adjusted for application during pregnancy, rather than after childbirth.

The MCA will review and discuss the identified risk factor(s) upon completion of the electronic assessment by the participant. Specific risk factors are linked to specific care pathways, which guide the MCA into taking appropriate action, and organize client-tailored care during pregnancy and the postpartum period. Care pathways consist of different steps a MCA can take to initiate a risk-guided provision of care in collaboration with professionals from different echelons. These steps can include communication with an involved community midwife or obstetrician but also with professionals from the public health sector. Care pathways are tailored in order to accommodate practice variations within maternity care organizations to fit local protocols and habits.

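### The stated effect model names no baseline covariate, although an antenatal MEQ and risk profile are collected in both arms and women are recruited after cluster allocation

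*Protocol article*

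**What the plan says.** All points are from the Methods of the protocol article.

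- **Model.** Statistical methods: "We will analyze the effect of the intervention on our primary and secondary outcome measurements using multilevel mixed-effects linear or logistic regression analyses", with a random effect assumed for each cluster. No fixed covariate is named. The preceding sentence plans chained-equation imputation of missing baseline characteristics but does not say what the imputed variables are for.
- **Intake data.** The electronic assessment contains Mind2Care, "the Maternal Empowerment Questionnaire (MEQ) [20] with slight modifications", and eight further questions on finances, insurance and earlier care use (Intervention at the level of the participant). Two of the five MEQ domains are dropped and the rest are reworded for pregnancy. The MCA discusses the results only once the woman has finished, so the data precede tailored care.
- **Both arms.** Control situation: "the risk assessment during pregnancy is performed in both study arms". The stated purpose is an adequate comparison of the arms on their risk factors.
- **Recruitment.** On the MCAs of participating organisations, Criteria for health care professionals says: "They will inform potential participants about the study and obtain written informed consent". Under Blinding: "Study information to participants strictly contains information related to the allocated arm".
- **Knowledge of the arm.** Control MCAs are told not to discuss detected risks. Intervention MCAs receive an extra training session.
- **Clusters.** Study setting: ten clusters, one intervention and one control in each of five (merged) municipalities.

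**The concern.** Randomising organisations balances organisations. It does not protect against differences in who is enrolled afterwards. Information that differs by arm can only be given once the arm is known, so consent follows allocation. MCAs with arm-specific instructions or training can hardly be unaware of their arm. Both are inferences from the text, but strong ones. Enrolment then turns on a consent conversation led by those MCAs, and no safeguard against differential recruitment is described. Five clusters per arm also give weak protection against chance imbalance.

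The intake assessment would let the analysis correct for whatever part of such imbalance it measures. A model with only arm and a cluster effect would not use it, and the imbalance would be read as treatment effect. If covariates are instead chosen after the imbalance has been seen, the choice becomes data-driven.

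**Working it through.** **1. The plan's own sample size.** Inputs, from Sample size and Statistical methods: "a proportion difference from a low empowerment score at the 20th centile towards the 10th centile", that is 20% against 10%; "two-sided statistical significance assessed at the 5% level"; 80% power; ICC 0.05; 33% loss.

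- n per arm = (1.960 + 0.842)² × (0.20×0.80 + 0.10×0.90) / 0.10² = 196.2. The article: "At an alpha of 0.05 and 80% power, we will require 196 participants per arm and as such 392 participants in total".
- Variance inflation = 1 + (196/5 − 1) × 0.05 = 1 + 38.2 × 0.05 = 2.91.
- Target = 1.5 × 2.91 × 196 = 855.5, rounded to 856 per arm.

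The figures reproduce. No covariate enters, so the stated power neither depends on adjustment nor takes credit for it.

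**2. Bias from a measured imbalance.** The article gives neither the correlation r between antenatal and postpartum MEQ nor any expected imbalance d. Both are assumed. Take a normal score underlying the outcome, cut at the control arm's 20th centile (z = −0.842), and no true effect. If intake MEQ is d SD higher in the intervention arm, the apparent prevalence there is Φ(−0.842 − r×d).

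| r | d = 0.1 | d = 0.2 | d = 0.5 |
|---|---|---|---|
| 0.3 | 0.8 points | 1.6 | 3.9 |
| 0.5 | 1.4 | 2.7 | 6.3 |
| 0.7 | 1.9 | 3.7 | 8.3 |

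Example: r = 0.5, d = 0.2 gives Φ(−0.942) = 0.173, and 0.200 − 0.173 = 2.7 points. At d = 0.2 the spurious difference is 16 to 37% of the 10-point target. An imbalance the other way would hide benefit to a similar degree.

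**3. Does adjustment remove it?** Simulation: 2 × 5 clusters, 114 women each, latent ICC 0.10 to approximate a binary ICC of 0.05, cluster-level t-test on 8 df, pairing ignored, 2000 runs. With d = 0.2 and no effect:

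| r | Mean difference, unadjusted | Adjusted | Type I error, unadjusted | Adjusted |
|---|---|---|---|---|
| 0.3 | −1.6 points | −0.1 | 0.057 | 0.052 |
| 0.5 | −2.5 | 0.1 | 0.061 | 0.043 |
| 0.7 | −3.5 | −0.1 | 0.092 | 0.054 |

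The bias disappears, as it must when the whole imbalance lies in the measured score. With a simulation error of about √(0.05×0.95/2000) = 0.005, only the type I error at r = 0.7 is clearly raised.

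**4. Precision.** Analysed women per cluster: 2.91 × 196 / 5 = 114.07. The design effect at that size is 1 + 113.07 × 0.05 = 6.65. (It differs from 2.91 because the plan uses 39.2 women per cluster; that is a separate matter.) The between-cluster part is 114.07 × 0.05 = 5.70, or 86%; the within-cluster part is 0.95.

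- *Only within-cluster variance explained:* variance ratio = (5.70 + 0.95 × (1 − R²)) / 6.65. R² = 0.09 gives 0.987 and R² = 0.36 gives 0.949, a fall of about 1 to 5%.
- *Both levels explained equally:* ratio = 1 − R², that is 0.91 to 0.64. This is an upper bound.

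In power terms, the effective n is 570.36 / 6.65 = 85.7 per arm and z = 0.10 / √(0.25/85.7) = 1.852, so power is about 46%. Dividing z by the square root of the variance ratio gives 46 to 48% in the first case and 49 to 64% in the second. In simulation, where the covariate explained only within-cluster variance, adjustment changed power by at most 0.006 (0.431 to 0.429, 0.380 to 0.386, 0.401 to 0.406).

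**The case against.** The strongest objection is that the article is silent on covariates, and that a covariate list commonly sits in an analysis plan or full protocol, neither of which is shown. A reader might infer that the trial has chosen an unadjusted model. The text does not say so, and imputing baseline characteristics has little purpose unless they enter some model. This stands: the point can only be that no covariate is named. It is still worth raising, because the article does fix the model form and the imputation, leaves the imputed variables without a stated role, and describes a recruitment process that makes that role matter.

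A reader might also infer that recruitment imbalance exists and goes uncorrected. The documents do not show this, and some features limit it. All women with a scheduled home visit are to be invited. The participant information mentions neither the randomised design nor the change in care. Each municipality contributes one cluster to each arm. These reduce selective approach and self-selection, but the consent step stays with MCAs who know their arm.

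A third tempting inference is that adjustment would lift power from 46% to as much as 64%. That needs the covariate to explain cluster means as well as it explains women within clusters, and nothing in the article supports this. It also uses the R² of a continuous score, whereas the outcome is dichotomised, which lowers R².

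Finally, the intake MEQ (three reworded domains) is not the same measure as the four-domain postpartum score. That weakens the expected correlation but does not disqualify it as a covariate.

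**Conclusion.** The point holds as one about prespecification. The stated effect model names no baseline covariate in a design that recruits after allocation into five clusters per arm, although suitable intake data exist in both arms. Bias is the main reason to act: 1.6 to 3.7 points against a 10-point target, if there is a 0.2 SD imbalance in intake MEQ, a correlation of 0.3 to 0.7, and no adjustment. All three are conditions, not facts in the article. Precision is a minor reason: a 1 to 5% fall in variance is the cautious expectation for R² of 9 to 36%, and more only if cluster means are also explained. Adjustment corrects measured imbalance only, so selection on unmeasured factors would remain. Confidence is medium, because the article is silent and an unseen document may already name the covariates.

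**What to change.** In Statistical methods, state that:

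- the primary model adjusts for the intake MEQ score (for example the three-domain mean) and a short prespecified set of intake factors, such as parity and the number of non-medical risk factors;
- each secondary model adjusts for the matching intake value where the intake assessment records one;
- the imputed baseline characteristics are the ones used as these covariates;
- the estimate without covariates is reported as a sensitivity analysis.

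Add a note that the adjusted odds ratio is conditional on the covariates. It can differ from the unadjusted one without any imbalance, so a gap between the two is not by itself evidence of selection. A standardised prevalence difference alongside it would keep the link to the 20% against 10% of the sample size.

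The cost is analysis wording only. The assessment is already done in both arms, imputation of missing baseline values is already planned, and parity should be known to the organisations because usual practice sets the form of the intake by it. The list should be fixed before outcome data are compared by arm.
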